**Methods:**

This exploratory study, followed by a noninferiority, investigator-blinded randomized clinical trial, will be divided into three phases: (1) development and validation of a sensor for real-time biofeedback during a functional assessment test; (2) integration of biofeedback and gamification into an app for the structured prescription of physical training within a controlled setting; and (3) implementation of biofeedback and gamification into an app for the prescription and monitoring of physical training in an uncontrolled setting. Phase 1 entails a validation test of a biosensor—monitoring heart rate (HR) and steps—during a modified shuttle walk test. In phase 2, the biosensor interfaces with a gamified smartphone application. The training regimen spans 6 weeks, 5 days weekly, with each session lasting 60 min: a five-min warm-up involving stationary gait, followed by 50 min of training at the target HR on the step and concluding with a five-min cool-down at a stationary pace. After 6 weeks of training, a new functional capacity test is conducted. Phase 3 involves an investigator-blinded, randomized clinical trial to demonstrate noninferiority. Participants are randomly assigned to either the intervention group (IG) or the control group (CG). IG participants practice exercise using the gamified application in an uncontrolled environment according to the prescribed method outlined in phase 2. CG participants receive PA practice guidelines exclusively.

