## Interventions

### Explanation for the choice of comparators {6b}

The World Health Organization recommends engaging in physical activity as a preventive measure against various diseases and for promoting overall health. This recommendation will be implemented within the control group.

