### Phase 3: Evaluation of gamified in uncontrolled environment

Phase 3 comprises a noninferiority, investigator-blinded, randomized clinical trial with two distinct groups: the intervention and control groups. Participants within the intervention group (IG) will install the gamified application on their smartphones and use a biosensor during exercise sessions. These sessions will align with the prescribed intensity derived from the ISWT, following the 6-week regimen detailed in phase 2. Participants will be duly instructed to cease exercising if they experience symptoms like chest pain, discomfort, or dizziness.

Within the gamified application, participants will have access to a diary feature, enabling them to log notifications received and their efforts during exercise, both monitored by the biosensor and the gamified app. On the other hand, individuals in the control group (CG) will receive instructions to engage in physical activity at home without biosensor monitoring. They will use the app independently, aiming for a minimum of 300 min per week at moderate intensity or at least 150 min per week at vigorous intensity (self-assessed).

Preceding and following the 6-week period, both the IG and CG will undergo assessments akin to those conducted in phase 1. These include evaluations of functional capacity, muscle oxygenation, and further assessments led by trained and blinded researchers.

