### Sample size {14}

Since phases 1 and 2 consist of a pilot study for the clinical evaluation of a biosensor prototype and the gamified application that considers a biofeedback system for performing physical exercises, a convenience sample of 15 individuals without medical contraindications for PA will be studied. Assuming a sample loss of 30%, we will recruit 20 participants.

The third phase will be a noninferiority, investigator-blinded randomized clinical trial of the individuals eligible for the study—considering the same eligibility criteria as in phases 1 and 2, in addition to being sedentary—will be divided into two groups: the intervention group (IG), which will receive the exercise protocol through the biosensor and gamified application, and the control group (CG), which will only receive guidelines for performing PA. Considering a confidence level of 95%, power of 80%, ratio of 1:1 between the CG and IG, and estimated prevalence of adherence to the protocol of 70% and 50% for the IG and CG, respectively, it would be necessary to allocate 104 individuals in each group. Adding 30% for possible follow-up losses, 149 sedentary individuals will be assigned to each group, totalling 298 subjects in the study.

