### Plans to promote participant retention and complete follow-up {18b}

Since one of the study’s goals is to assess the impact of gamification on adherence to PA, no specific measures will be undertaken during the study to bolster adherence. Upon the study’s conclusion, all participants will be contacted for a final assessment. For measuring adherence, the intervention group will register their adherence via a dedicated application. Meanwhile, the control group will be guided to record their physical activities on a weekly basis added to plans to promote participant retention and complete follow-up.

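### The control arm is described both as guidelines only and as using the app, so the randomised contrast is not fixed and the 50% control adherence rate supports only one of the two versions

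*Protocol article*

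**What the plan says.** Two places in the protocol article give controls advice and nothing more. The abstract (Methods) states: "CG participants receive PA practice guidelines exclusively". Sample size {14} describes the control group as the one "which will only receive guidelines for performing PA", in the same paragraph that sets adherence at 70% in the intervention group and 50% in the control group.

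The section Phase 3: Evaluation of gamified in uncontrolled environment is the only operational description of the two arms. Intervention participants "will install the gamified application on their smartphones and use a biosensor during exercise sessions". Controls "will receive instructions to engage in physical activity at home without biosensor monitoring", and then: "They will use the app independently, aiming for a minimum of 300 min per week at moderate intensity". The article describes no second app, so the natural reading is that this is the gamified application.

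On recording, section {18b} says that "the intervention group will register their adherence via a dedicated application", while controls are to keep a weekly record of their activity. Section {11c} adds a weekly message asking both groups to fill in a spreadsheet.

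On purpose, {18b} says that "one of the study’s goals is to assess the impact of gamification on adherence to PA", and {11c} calls adherence facilitated by gamification one of the primary objectives. Between-group adherence is one of the listed primary outcomes in Outcomes {12}.

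**The concern.** A control arm that receives only guidelines cannot also use the app. The conflict sits in the definition of the comparator, and it lies in the section that study staff would consult to learn what to deliver.

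Two things depend on the answer. The first is the question that the trial answers. If the app is in both arms, the arms differ by the biosensor, and the comparison says nothing direct about whether gamification raises adherence. The second is the sample size. The 50% control rate is given for people who receive advice. An app built to promote adherence could plausibly raise that rate, and the planned 20-point difference would shrink accordingly. If delivery varied between participants because the text was ambiguous, the analysis could not repair it.

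**Working it through.** **Step 1. The two versions side by side**

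| | Guidelines-only version | App-using version |
|---|---|---|
| Where stated | Abstract (Methods); Sample size {14} | Phase 3 description |
| Intervention arm | App + biosensor | App + biosensor |
| Control arm | Activity guidelines | App, no biosensor, self-assessed intensity |
| What the contrast estimates | Effect of the app-plus-biosensor package | Added effect of the biosensor |
| Gamification goal in {11c} and {18b} | Addressed as part of the package | Not addressed |
| Recording in {18b} (application for intervention, weekly record for control) | Fits | Unexplained: controls would have the app but not register in it |
| 50% control adherence | Stated for this control | No support given |

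The spreadsheet request in {11c} goes to both groups. It is compatible with the guidelines-only version but does not by itself decide between the two.

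**Step 2. Reproduce the stated sample size**

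Inputs from Sample size {14}: 95% confidence (α = 0.05; sidedness is not stated), 80% power, 1:1 allocation, p₁ = 0.70, p₂ = 0.50. Here p̄ = 0.60 and d = 0.20.

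n = [1.960·√(2p̄(1−p̄)) + 0.842·√(p₁(1−p₁) + p₂(1−p₂))]² / d²

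= [1.960·√0.48 + 0.842·√0.46]² / 0.04 = (1.358 + 0.571)² / 0.04 ≈ 93 per group.

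With continuity correction: n′ = (n/4)·[1 + √(1 + 4/(nd))]² = (93/4)·[1 + √(1 + 4/18.6)]² = 102.8, or 103 per group, against 104 stated. The one-sided versions give 74 and 83, so the two-sided corrected test is the match. Losses: 104/(1 − 0.30) = 148.6, or 149, exactly as stated. The arithmetic is sound. It is a test of a difference, with no noninferiority margin in it.

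**Step 3. Illustrative power if app use raises control adherence**

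The documents give no adherence rate for app-using controls. The rates of 55% and 60% are assumptions: they give controls a quarter or a half of the planned 20-point benefit. The intervention rate stays at 70%, with n = 104 evaluable per arm.

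Power = Φ[(d − c − 1.960·se₀)/se₁], where se₀ = √(2p̄(1−p̄)/n), se₁ = √((p₁(1−p₁) + p₂(1−p₂))/n), and c = 0 without correction or 1/n with it.

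- Control 50%: se₀ = 0.0679, se₁ = 0.0665. Uncorrected (0.200 − 0.1332)/0.0665 = 1.01, power 84%; corrected 81%.
- Control 55%: se₀ = 0.0671, se₁ = 0.0663. Uncorrected (0.150 − 0.1316)/0.0663 = 0.28, power 61%; corrected 55%.
- Control 60%: se₀ = 0.0661, se₁ = 0.0658. Uncorrected (0.100 − 0.1296)/0.0658 = −0.45, power 33%; corrected 28%.

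If all 149 per arm contributed an adherence outcome, the uncorrected figures would be 94.5%, 76.5% and 44.0%.

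**Step 4. Size needed under the same assumptions** (two-sided, corrected, 80% power)

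- Control 55%: 176 evaluable per group; 176/0.7 = 251.4, so 252 with 30% losses.
- Control 60%: 376 evaluable per group; 376/0.7 = 537.1, so 538 with 30% losses.

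**The case against.** The strongest reply is that one sentence stands against the rest and may be a drafting slip. The abstract, the sample size section and the recording plan in {18b} all point to guidelines only. That may be so, but the text cannot settle it. All participants must own an Android smartphone, so controls could run the app. A slip in the operational description would still need correcting.

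Other parts of the case against limit how far the point goes. A reader might make these stronger inferences, which the documents do not support:

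- *That the 50% rate is undefined.* It is defined, for a guidelines-only control. It is unsupported only for a control that uses the app.
- *That the comparator rationale in {6b} also contradicts the app sentence.* It says "This recommendation will be implemented within the control group", which neither limits controls to guidelines nor mentions the app.
- *That a guidelines-only control would isolate gamification.* It would not, because the biosensor comes bundled with the app. The Discussion frames the hypothesis as gamification combined with wearables, so the package effect is a legitimate target, but it should be named as such. An app-without-biosensor control would also bear on part of that hypothesis.
- *That controls would certainly receive full gamification.* The article does not say how much of the game works without the biosensor. Full exposure is inferred from the wording.
- *That a null result would be uninterpretable.* Once the comparator is fixed, a null result speaks to that contrast, subject to power. It is hard to read only while the comparator is unstated.
- *That power will fall to 28–61%.* Those figures follow entirely from assumed control rates. They also treat the trial as a superiority comparison, as the calculation does, although the article labels it noninferiority.

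**Conclusion.** The contradiction is real and must be resolved. The Phase 3 description gives controls the app, while the abstract and the sample size section exclude it. The trial is therefore either a test of the app-plus-biosensor package against advice or a test of what the biosensor adds to the app. The second cannot address the gamification goal stated in {11c} and {18b}.

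The 104 and 149 per group are correctly calculated, but for the guidelines-only version. The loss of power under the other version cannot be known from the article. At assumed control rates of 55–60% it would be large, but the case for correction rests on the conflicting definitions and not on those figures. Which control condition is intended is for the investigators to say.

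**What to change.** State one control condition and use it in the abstract, the Phase 3 description and the sample size section.

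- **If guidelines only:** remove the app-use clause from the Phase 3 description, state that controls have no access to the gamified app during the 6 weeks, and describe the contrast as the effect of the app-plus-biosensor package. The cost is one sentence plus control of app downloads, with no added participants or procedures.
- **If app access is intended:** correct the abstract and Sample size {14}, restate the objective as the added effect of the biosensor, and restate the control adherence rate and the power with a justification. Align the control group's adherence recording in {11c} and {18b} with app use. This may cost participants: about 176 to 376 evaluable per group under the illustrative rates, against 104 now.

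Trial status schedules recruitment to the randomised trial from June 2023 to about December 2026. If randomisation has started, also document what control participants actually received, and from when.

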#### Endothelial function assessment

The evaluation of endothelial function will encompass two methods: pulse tonometry (EndoPAT2000, Itamar Medical, Caesarea Israel) [30–32] and ultrasonography to measure flow-mediated vasodilation (FMD) of the brachial artery (MyLab 70 Xvision, Esaote SpA, Florence, Italy) [33, 34].

#### Autonomic function assessment

The autonomic function of participants will be evaluated through the analysis of heart rate variability (HRV), involving the recording of R-R intervals utilizing the Polar H10 strap (Polar Electro Oy, Kempele, Finland) [21].

For HRV analysis, the time series of RR intervals, acquired from the Polar recordings, will undergo interpolation and decimation. This process aims to generate a time-equally spaced series, subsequently subjected to fast Fourier transformation (FFT) using a MATLAB-based algorithm (MATLAB 6.0, Mathworks Inc., USA). The spectral power will be calculated by integrating within each specified frequency band of interest. The RR time series will be explored in both time and frequency domains, including low frequency (LF), high frequency (HF), and very low frequency (VLF). This will yield parameters related to variability and autonomic balance.

In the time domain, computed parameters will encompass mean RR interval values, standard deviation, and the square root of the sum of the squares of successive differences (rMSSD).

### Criteria for discontinuing or modifying allocated interventions {11b}

Physical exercise may lead to effects such as increased heart rate, sweating, fatigue, minor discomfort related to equipment use, discomfort in the lower limbs, and mild muscular fatigue after treadmill training. In the event of any of these mentioned episodes occurring, whether during assessments or physical training, researchers will halt the protocol and provide initial assistance if necessary. If the participant stabilizes and agrees, the protocol may be resumed.

During the execution of training in an uncontrolled environment (phase 3), participants will be advised to discontinue the protocol if any discomfort or symptoms arise. They should await the cessation of these symptoms. If conditions permit, participants should resume from where they left off. If there is no improvement, they will be instructed to contact the researchers via telephone for appropriate measures.

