### Eligibility criteria {10}

The recruitment of individuals will adhere to specific inclusion criteria: (i) individuals aged between 20 and 60 years without medical contraindication to engage in physical exercise, (ii) possession of a smartphone (cell phone with Android operating system), and (iii) willingness to participate in the research by signing the informed consent form. The exclusion criteria were experience angina during exertion, history of acute myocardial infarction within the 12 months prior to the start of the protocol, require oxygen supplementation, exhibit clinical instability in the month preceding the protocol initiation, uncontrolled hypertension, visual diseases that prevent the performance of the protocol, chronic conditions hindering participation in the exercise protocol, illiterate, and refuse to sign informed consent form.

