#### Prescription of physical exercise

Building upon the ISWT results, the intensity of physical exercise will be tailored. The training protocol will span six weeks, with sessions conducted 5 days a week. The training volume will encompass a minimum of 300 min weekly at moderate intensity (40–60% of heart rate reserve) or a minimum of 150 min weekly at vigorous intensity (60–80% of heart rate reserve) [26]. The training will involve a one-step staircase (20 cm height, 60 cm length, and 40 cm width). The target intensity will range from 40 to 80% of the heart rate reserve, calculated based on ISWT. The heart rate reserve will be determined by subtracting the resting heart rate from the maximum heart rate achieved during the functional test. Throughout the exercise session, both HR monitors (Polar H10) and the test biosensor will be closely monitored.

The gamified smartphone application will offer visual feedback on intensity and heart rate, alongside researcher observation of heart rate measured by Polar H10 and the biosensor linked to the gamified application. Additionally, the biosensor, equipped with an accelerometer, will track step count during training. Phases within the scenario will be defined using gamification techniques, incorporating rewards, competitions, and other strategies to ensure adherence and engagement across varying intensities, including warm-up, maintenance, and cool-down phases.

In the initial week, sessions will last 30 min: a 5-min stationary gait warm-up, 20 min of step interval training (2 min at target HR and 3 min at low intensity), and a 5-min stationary gait cool-down. Over the subsequent 5 weeks, each session will extend to 60 min: a 5-min stationary gait warm-up, 50 min of step training at target HR, and a 5-min stationary gait cool-down. Sessions will occur at least twice a week and no more than five times. To meet the minimum adherence criterion, participants must achieve at least 70% of the prescribed training volume outlined in the protocol. Upon completing the 6-week training program, a new functional capacity assessment will be conducted.

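### In unsupervised phase 3 training, chest pain or dizziness that settles with rest may be followed by more exercise without any contact with the team

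*Protocol article*

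**What the plan says.** The rule for phase 3 is in the protocol article, section {11b}, second paragraph. In training away from the laboratory, "participants will be advised to discontinue the protocol if any discomfort or symptoms arise". They then wait for the symptom to pass. Next, "If conditions permit, participants should resume from where they left off". Last comes the only prompt to contact the team: "If there is no improvement, they will be instructed to contact the researchers via telephone for appropriate measures".

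Warning symptoms are named elsewhere, in the description of phase 3: "Participants will be duly instructed to cease exercising if they experience symptoms like chest pain, discomfort, or dizziness". That sentence says nothing about restarting or reporting, and neither section refers to the other.

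The Eligibility criteria {10} list "experience angina during exertion" among the exclusions. Under Sample size {14}, phase 3 participants must also be sedentary.

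On training load, the section on prescription of physical exercise states: "The target intensity will range from 40 to 80% of the heart rate reserve". It also states: "Sessions will occur at least twice a week and no more than five times". The phase 3 description applies that regimen to the intervention group. It lets the control group choose vigorous exercise, judged by the participant and without the biosensor.

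**The concern.** The prompt to phone depends on whether a symptom persists and takes no account of what the symptom is. Chest pain that comes on with effort and goes away with rest is the pattern that the exertional angina exclusion is meant to keep out of the trial. Because it settles, it never triggers the call. A participant who would have been excluded had the symptom been known at entry is therefore directed back to exercise, subject only to their own view of whether conditions permit, a phrase that is not defined.

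The population makes this relevant. Sedentary people are starting structured training, so an exertional symptom may first show itself then. Entry exclusions and the baseline shuttle walk test lower the risk, but they cannot detect a symptom that begins during the 6 weeks. What is at stake is participant safety. No endpoint or power calculation is affected.

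**Working it through.** **Reading the two instructions together**

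| Question | Phase 3 description | Section {11b}, phase 3 paragraph |
|---|---|---|
| Which symptoms? | Chest pain, discomfort and dizziness, as examples | Any discomfort or symptom |
| Stop? | Yes | Yes |
| May exercise resume? | Not addressed | Yes, after the symptom ceases, if conditions permit |
| Who decides? | Not addressed | The participant; no one else is mentioned |
| When is the team contacted? | Not addressed | Only if there is no improvement |

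For a symptom that settles, no cell in the table requires contact or review before exercise resumes. Where researchers are present, section {11b} has them halt the protocol and assist if needed, and resumption then requires that the participant has stabilised and agrees. No comparable check exists at home.

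**Other provisions that might catch the episode**

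- Adverse event reporting {22}: events are to be documented, but no route or timing is given by which a symptom resolved at home reaches the team.
- Strategies to improve adherence {11c}: the weekly message to both groups asks for a record of activity, not of symptoms.
- App diary: it logs notifications and effort. The statistical methods {20a} plan a qualitative analysis of diary reports, with no review before the next session described.
- Auditing {23}: monitoring of trial conduct is monthly.
- Final assessment ({13}, {18b}): it takes place after the 6 weeks.

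**Exposure left after a symptom that settles, intervention group**

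Inputs, all from the section on prescription of physical exercise: 6 weeks; k = 2 to 5 sessions per week; 30 minutes per session in week 1 and 60 minutes in weeks 2 to 6, warm-up and cool-down included.

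- Total sessions N = 6k. For k = 2, N = 12. For k = 5, N = 30.
- Total minutes = 30k + 5 × 60k. For k = 2: 60 + 600 = 660 min = 11.0 h. For k = 5: 150 + 1,500 = 1,650 min = 27.5 h.
- Left after the first session, sessions: N − 1 = 11 (k = 2) or 29 (k = 5).
- Left after the first session, time: 660 − 30 = 630 min = 10.5 h, or 1,650 − 30 = 1,620 min = 27.0 h.
- Average sessions left if onset is equally likely in any session: (N − 1)/2 = 5.5 (k = 2) or 14.5 (k = 5).

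Control-group session counts are not stated, so no matching figure is given. The article has no figure of its own on this point to reproduce.

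**The case against.** The best counter-argument is that the two sections divide the work. Section {11b} opens with ordinary effects such as sweating, fatigue and leg discomfort, for which stop, wait and resume is sensible. Chest pain and dizziness appear only in the phase 3 description, where the instruction is to cease, with no resume step. On that reading, warning symptoms are already under the stricter rule. The reading is possible, but the list of ordinary effects belongs to the paragraph on sessions with researchers present. The phase 3 paragraph that follows covers any symptom and makes no exception, and the supposedly stricter sentence still does not bar resumption or require contact.

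Other points carry some weight:

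- Resumption is conditional, and participant materials that are not shown may say more. This would not correct the sequence printed in the article.
- Absolute risk is probably low. Participants are aged 20 to 60 and screened, intervention-group intensity is set below the maximum heart rate reached in the shuttle walk test, and week 1 is interval work.
- The session counts measure the length of the schedule, not risk. They assume that training continues and nobody is told. The low end, two 60-minute sessions or 120 minutes a week, also falls below the weekly minimum of 150 or 300 minutes in the same section, so it is a floor.
- The sentence naming chest pain stands in the intervention-group paragraph, so its reach to the control group is uncertain. The wording of section {11b} is general and covers both arms.

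These points limit the size of the concern. None adds a check before exercise resumes.

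**Conclusion.** The concern holds. The published rule prompts a call only when a symptom fails to improve, so chest pain or dizziness on exertion that settles with rest may be followed by resumed exercise without review, in either arm. In the intervention group, a first-session symptom leaves 11 to 29 further scheduled sessions (10.5 to 27.0 hours) before the next scheduled assessment. The average is 5.5 to 14.5 sessions if onset is equally likely in any session. Those figures rest on the stated range of two to five sessions per week, on the participant completing the schedule, and on no call being made unprompted. They measure exposure; with no symptom or harm rate in the article, an expected number of events cannot be given. The rule should be corrected on safety grounds, but the low absolute risk and the absence of any effect on the trial's inference keep it below the most serious class of problem.

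**What to change.** Amend the phase 3 paragraph of section {11b}, with a cross-reference to the phase 3 description, along these lines: in either arm, a participant who has chest pain, dizziness or syncope during exercise stops and contacts the team before any further exercise, even if the symptom has gone. Keep the present stop, wait and resume rule for ordinary effects such as fatigue or leg discomfort.

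The cost is one sentence, one cross-reference and a few more calls to the team over the 6 weeks. A safety call made by the participant is not the proactive adherence contact that section {18a} rules out, so the adherence outcome should be little affected.
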